#### Costing and cost-effectiveness assessment

First, costing will be undertaken from a societal perspective. Data on OOP expenditures for accessing MNCH services such as ANC, institutional delivery and curative care (including outpatient consultation and hospitalization) during the neonatal and infancy period will be collected during the CEAHH survey. A bottom-up costing method will be used to collect data on health system costs of implementing the m-health application as in the ReMiND project. This will comprise data on start-up costs such as planning meetings, development of software, and training of ASHAs. The initial start-up costs (such as trainings and software development) will be considered as capital costs and will be annualized based on the expected life of the product produced. Second, these will be apportioned to the two blocks of UP, assuming a scenario that the application can be scaled up in all of UP without further adaptation. Cost of implementation of the program will be assessed in terms of resources of implementing partners such as CRS and Vatsalya, which implemented the program in the intervention area. These resources include staff salaries, equipment, building and space, drugs and consumables, and other overheads. Health system costs for delivering services through ASHAs will be assessed by collecting data on performance-based incentives paid to the ASHAs. For the purpose of cost scale-up analysis, only those start-up costs will be considered that are likely to be incurred by the health system as part of scale-up – for example, adaptation of the software in the new state, trainings, and any manuals to be developed.

Other health system costs that are incurred for delivery of preventive and curative MNCH services will be drawn from published studies (26–28). Together with data on health service utilization and OOP expenditures (as obtained from the CEAHH survey), epidemiological parameters (as obtained from a review of literature) and data on health system costs collected from the present study, overall cost of delivering MNCH health services will be estimated. This will also be used to generate the estimate for standardized cost of delivering MNCH services (preventive and curative) at the district level, with and without the m-health application.

An existing model to evaluate the impact of IMNCI would be adapted and used to undertake the cost-effectiveness analysis (29). A decision model will be developed using an MS-Excel spreadsheet to estimate the incremental cost-effectiveness of implementing the m-health application for ASHAs as used in the ReMiND project (Figs. 2–4). A time horizon of 10 years starting from base year 2011 was considered appropriate to cover all costs and effects comprehensively. Ideally, period of time horizon should be such that it covers all important costs and consequences as a result of the intervention. In the case of ReMiND project, several reasons justify the time horizon of 10 years. First, the m-health software is unlikely to change in this period as the broad nature of services will remain same. Second, based on expert opinion even if the software has to be edited based on revisions in the program package, such changes are unlikely to have any major cost implications. Third, the health system programs also have a shelf life, and it has been observed that incremental changes in the program design are usually made over an approximate 10-year period. However, majority of the diseases show their effects in the childhood period, that is, 0–5 years of age and some other disease may take even longer (10 years) to show their effects. In view of both situations, we believe that a 10-year time horizon will be appropriate to account for all the costs and benefits that accrue as a result of the intervention.

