## Background

### Study setting

The study will be conducted in the Kaushambi district in UP. Out of the district's eight community development blocks, the m-health intervention has been implemented in two blocks: Mooratganj and Manjhanpur.

The Catholic Relief Services (CRS) with the help of a local NGO, Vatsalya, introduced the CommCare m-health application to 259 ASHAs in the two intervention blocks in 2012. The ASHAs in the ReMiND project were provided with basic Java-based mobile phones operating on open source CommCare software (15). Extensive trainings of ASHAs were done in both blocks on the use of these phones. The ReMiND application has tailored content and guides the ASHA through the course of a woman's pregnancy and newborn child care. ASHAs use the application for the following purposes:To register each pregnant womanTo update her ANC record during home visits on the mobile applicationTo track her from pregnancy into the postpartum periodTo track the health of the newbornTo track the status of routine immunization until 2 years of ageTo provide appropriate counseling and support at each of these stepsThe phones contain locally relevant audio and visual prompts to help ASHAs navigate through the application. These recordings and pictures enrich the counseling experience of ASHAs during their home visits. The application uses the data entered about the pregnancy to guide ASHAs in providing timely and appropriate health information; it helps them to prioritize home visits; and it employs algorithms to assist in the early identification, treatment, and rapid referral to appropriate care of any danger signs among pregnant women or neonates (Fig. 1). While ASHAs have many tasks assigned to them, the key one is to identify pregnant women and visit them throughout the course of their pregnancy, seeing them through delivery in a safe facility and appropriate newborn care.

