### Overview of study design

The study has been approved by the Institute Ethics Committee of the Post Graduate Institute of Medical Education and Research, Chandigarh, India. Written informed consent will be obtained from all study participants. Administrative approval will be obtained for collection of relevant data.

We will use a quasi-experimental design comprising pre- and post-intervention observations with a control to assess the impact of the ReMiND project. Data from the Annual Household Survey (AHS) undertaken by the Registrar General of India in district Kaushambi in 2011 will be used for baseline or pre-intervention assessment (4). The AHS is the largest demographic survey in the world and covers two and a half times that of the Sample Registration System (India's most regular source of demographic statistics). The sampling design adopted for the AHS is a uni-stage stratified simple random sample without replacement, except in case of larger villages in rural areas (i.e. having a population greater than or equal to 2000 as per 2001 census), wherein a two-stage stratified sampling procedure has been applied. The details of the AHS survey are incorporated in the supplementary material.

We will undertake a cost-effectiveness analysis household (CEAHH) survey in 2015 in two intervention blocks and two control blocks from the Kaushambi district to assess the coverage of various MNCH services that represent the post-intervention status. To carry out the CEAHH survey, two structured interview schedules were developed after an extensive review of existing tools used in AHS, the National Family Health Survey, the District Level Household Survey, and the Coverage Evaluation Survey.

Together, the AHS and the CEAHH will be used to assess the impact of the ReMiND m-health intervention using a difference in differences (DID) analysis. To reduce selection bias, before DID is performed, propensity score matching (PSM) will be used to match the cases from the intervention blocks with those in the control group based on their socio-demographic characteristics, for the period between 2011 and 2015 (4). Further, subgroup analysis will be done to analyze the impact of intervention among various levels of underlying factors, such as the mother's education and the occupation of the head of household.

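### As worded, the start-up cost rule spreads ASHA training over an assumed roll-out to all of Uttar Pradesh, which understates the cost per DALY averted in the two blocks

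*Protocol article*

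**What the plan says.** All of the rule stands in the section Costing and cost-effectiveness assessment of the protocol article. The bottom-up costing collects the start-up items: "This will comprise data on start-up costs such as planning meetings, development of software, and training of ASHAs". The next step capitalizes them: "The initial start-up costs (such as trainings and software development) will be considered as capital costs and will be annualized". The sentence after that sets the allocation: "these will be apportioned to the two blocks of UP, assuming a scenario that the application can be scaled up in all of UP", on the premise that the application would need no further adapting.

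The same section has a separate rule for the scale-up analysis, under which "only those start-up costs will be considered that are likely to be incurred by the health system as part of scale-up". Trainings are among the examples given there.

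On where the training took place, Study setting says that the implementing organizations "introduced the CommCare m-health application to 259 ASHAs in the two intervention blocks in 2012", and adds: "Extensive trainings of ASHAs were done in both blocks on the use of these phones". On where the effects come from, Overview of study design places the post-intervention survey "in two intervention blocks and two control blocks from the Kaushambi district to assess the coverage of various MNCH services". Objectives lists the cost per DALY averted against routine services and the cost of scale-up as separate aims.

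**The concern.** Software is a fixed cost. Once built, it can serve more blocks at little extra expense, so charging two blocks a share of it is a defensible and openly declared choice. Training grows with the number of workers trained. The 259 ASHAs had to be trained for the two blocks to show any effect, and training them does nothing for other blocks.

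If that cost is apportioned together with the software, the numerator carries only part of what it took to produce the effects in the denominator. The error can run only one way, towards a lower cost per DALY averted. The cost per unit of composite coverage rests on the same costs and would move the same way. The Discussion says that the results are meant to help state and national government decide on replication, so a one-sided error in the main economic ratio matters.

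**Working it through.** The plan states no cost, ratio or allocation key, so there is no figure to reproduce. The check has two parts.

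**Which items the rule covers**

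1. The sentence just before the apportionment names its subject: "The initial start-up costs (such as trainings and software development) will be considered as capital costs". The pronoun in the apportionment sentence refers back to these costs, and trainings are named among them.
2. Nothing elsewhere in the article exempts training.
3. The stated premise concerns adapting the application. It is a reason to share software and gives none for sharing training.
4. The scale-up rule counts trainings as incurred when the programme expands. A cost that has to be met again in each new area is not a one-off that the state shares.

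**Direction and illustrative size**

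Let T be the annualized training cost of the two blocks, f the fraction of T charged to them, D the DALYs averted there, and C the net incremental cost with T charged in full.

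- Shortfall in the ratio = T(1 − f)/D. This is above zero whenever T > 0 and f < 1.
- With s = T/C and C > 0: reported ratio / ratio with training in full = 1 − s(1 − f).

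Inputs that are assumptions:
- Key: f = 2/B, where B is the number of blocks in the state. The article gives neither this key nor B.
- Low B: 19 high focus districts (Theory of change) × 8 blocks, as in Kaushambi (Study setting) = 152, so f = 2/152 = 1.3%.
- High B: 1,000, so f = 2/1,000 = 0.2%.
- s from 5% to 50%.

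| s | Reported / full, B = 152 | Full / reported, B = 152 | Reported / full, B = 1,000 | Full / reported, B = 1,000 |
|---|---|---|---|---|
| 5% | 0.951 | 1.05 | 0.950 | 1.05 |
| 10% | 0.901 | 1.11 | 0.900 | 1.11 |
| 20% | 0.803 | 1.25 | 0.800 | 1.25 |
| 30% | 0.704 | 1.42 | 0.701 | 1.43 |
| 50% | 0.507 | 1.97 | 0.501 | 2.00 |

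Worked line: s = 20%, B = 152 gives 1 − 0.20 × (1 − 0.0132) = 0.803, and 1/0.803 = 1.25.

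Under this key the result hardly depends on B. It depends almost wholly on s, which the article does not allow one to estimate.

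**The case against.** The strongest reply is that the authors meant software only. The premise about adaptation is software language, and so is annualizing over the life of the product. Since the section counts trainings again at scale-up, the authors evidently know that training is not shared. This is a plausible account of their intent. What stands of it is that the defect may be one of wording. But the sentence names trainings, and an analyst who follows it would apportion them.

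A second reply concerns the key. The article says that costs are apportioned but not how. If the pool were the training of every ASHA in the state, the two blocks' share would be roughly their own training cost and the bias would largely vanish. No such pool is described, however: the costs to be collected are those of the project as implemented. The reply does show that 2/B is only one possible key. A reader might infer that nearly all training cost drops out of the ratio; the article does not fix the key, so it does not support that.

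A third reply is that training may be a minor item. The numerator also holds household spending, ASHA incentives and the cost of preventive and curative services, so training's share of net incremental cost could be small. This stands in full.

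**Conclusion.** The concern holds for the rule as written. Apportioning the two blocks' training cost over an assumed state-wide roll-out, while the DALYs are those of the two blocks, understates the incremental cost per DALY averted. The direction needs only that training cost is above zero and that the share charged is below one.

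The size is unknown. The factors of about 1.05 to 2.0 are illustrations that rest on an assumed training share of 5% to 50%, the assumed 2/B key, fixed DALYs and a positive net incremental cost.

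A reader might go further and put the understatement at the whole start-up share of programme cost. The document does not support that. It gives no such share, part of start-up is software that may fairly be shared, and programme cost is not the net incremental cost in the ratio. Nor is apportionment of software an error. The only sensitivity analysis that the article mentions concerns the weights of the composite coverage indicator, so nothing stated there would bring this problem to light.

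**What to change.** In the costing section, state item by item which start-up costs are apportioned and by what key. In the base case, charge annualized ASHA training, and any planning specific to the two blocks, in full to those blocks. Apportion only software development and other costs that wider use truly shares. Report the ratio with no apportionment at all as a sensitivity analysis. Keep state-wide sharing of anything beyond software for the separate scale-up analysis. If software alone was meant from the start, rewording the sentence to say so is enough for the base case.

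The cost is small: a changed allocation key in the costing sheet, using items that the bottom-up costing already collects. The price is that the ratio becomes somewhat less favourable to the intervention.

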**Fig. 2 F0002:**
[figure not shown]
Decision model for cost-effectiveness study of m-health application for ASHA workers as part of ReMind project. Note: DH=district hospital, CHC=community health center, FRU=first referral unit, PHC=primary health center, SC=sub-center, ASHA=accredited social health activist, AWW=Anganwadi worker, MNCH=maternal neonatal and child health. Cycle repeated for 15 birth cohorts. Source: This model is adapted from a similar figure in Ref. (29).

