**Fig. 3 F0003:**
[figure not shown]
Outcome model for cost-effectiveness study of m-health application for ASHA workers as part of the ReMind project. Note: In continuation to the model 1, outcome model describes the probable scenarios after a neonatal or post-neonatal infant had been treated or not (irrespective of type of health facility). YLD=years of life lived with disability, YLL=years of life lost due to premature mortality, DALY=disability-adjusted life years. Source: This model is adapted from a similar figure in Ref. (29).

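### The decision model is given a 10-year horizon from 2011 but 15 birth cohorts, and one 10-year figure serves both as programme life and as follow-up per child

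*Protocol article*

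**What the plan says.** All references are to the protocol article.

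- *Costing and cost-effectiveness assessment*, horizon: "A time horizon of 10 years starting from base year 2011 was considered appropriate to cover all costs and effects comprehensively".
- Same section, the criterion for choosing a horizon: "Ideally, period of time horizon should be such that it covers all important costs and consequences as a result of the intervention".
- Same section, reasons for 10 years. The first three concern the programme: the software is expected to stay stable, edits to it should cost little, and health programmes are usually revised over about a decade. The next concerns disease: "majority of the diseases show their effects in the childhood period, that is, 0–5 years of age". A second, longer lag is then given for certain conditions: "some other disease may take even longer (10 years) to show their effects".
- Same section, conclusion: "we believe that a 10-year time horizon will be appropriate to account for all the costs and benefits that accrue".
- Note to Fig. 2, the decision model introduced in that section: "Cycle repeated for 15 birth cohorts".
- Note to Fig. 3, the outcome model: DALYs include years of life lost ("YLL=years of life lost due to premature mortality") and years lived with disability. No rule is given for cutting either at the horizon.
- *Study setting*, start of the intervention: the implementing partners "introduced the CommCare m-health application to 259 ASHAs in the two intervention blocks in 2012".

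**The concern.** Two things do not fit together.

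First, the number of birth cohorts and the horizon are both printed for one model, and they disagree. This is not detail that an article leaves to a fuller document, because both figures are given. The number of cohorts sets how many births are costed and credited with benefit.

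Second, programme life and disease lag answer different questions. Programme life says for how many years new mothers and children enter the model. Disease lag says how long each child must be followed after entry. One horizon can serve both only if it is at least the entry period plus the lag. Using the same 10 years for both leaves the reader unable to tell whether late cohorts are followed to the end of their lag or cut off at a common date. If they are cut off, their programme costs are counted while part of their benefit is not.

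Incremental cost per DALY averted is a stated aim under *Objectives*, and its result is meant to inform scale-up. The primary objective, the effect on service coverage, is not touched.

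**Working it through.** **Inputs.** Horizon H = 10 years from 2011 and lags L = 5 and L = 10 years (*Costing and cost-effectiveness assessment*); 15 cohorts (Fig. 2 note); introduction in 2012 (*Study setting*). The cycle length is not stated; one year is assumed.

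**Step 1: can 15 be reproduced?** Cohorts in the window = H / cycle length = 10 / 1 = 10, born 2011 to 2020. Fifteen annual cohorts run from 2011 to 2025, so 15 − 10 = 5 are born after the window closes. To fit 15 into 10 years the cycle would have to be 120 / 15 = 8 months, which the article nowhere suggests. The figure of 15 does not reproduce.

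**Step 2: follow-up under a fixed calendar window.** For the cohort born at the start of year 2011 + k, follow-up counted towards lag L is max(0, min(L, 10 − k)).

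- Ten cohorts, L = 5: k = 0 to 5 give 5 years each (30), and k = 6 to 9 give 4 + 3 + 2 + 1 = 10. The total is 40 of 50 cohort-years (80%). Six of 10 cohorts complete ages 0–5; 4 of 10 do not.
- Ten cohorts, L = 10: 10 + 9 + … + 1 = 55 of 100 (55%). One of 10 cohorts is followed for 10 years.
- Fifteen cohorts: the last five add nothing, so the shares are 40 of 75 (53%) and 55 of 150 (37%).

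**Step 3: sensitivity to the assumptions.**

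| Case | L = 5 | L = 10 |
|---|---|---|
| 10 cohorts from 2011, births at start of year | 40/50 = 80% | 55/100 = 55% |
| 10 cohorts from 2011, births at mid-year | 37.5/50 = 75% | 50/100 = 50% |
| 9 cohorts from 2012, births at start of year | 35/45 = 78% | 45/90 = 50% |
| 15 cohorts from 2011, births at start of year | 40/75 = 53% | 55/150 = 37% |
| 15 cohorts from 2011, births at mid-year | 37.5/75 = 50% | 50/150 = 33% |

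If only cohorts born from 2012 count as exposed, none is followed for 10 years and 5 of 9 complete ages 0–5.

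**Step 4: horizon needed to follow every cohort.** The last of n annual cohorts enters at n − 1 years, so the horizon must be (n − 1) + L. Ten cohorts need 9 + 5 = 14 or 9 + 10 = 19 years. Fifteen cohorts need 14 + 5 = 19 or 14 + 10 = 24 years. A 10-year window meets none of these.

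**Step 5: how much of the first year is lost?** With L = 1 and ten cohorts born at the start of each year, all ten complete infancy inside the window. With mid-year births, nine do and the tenth has half a year.

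**The case against.** The best defence is that a common end date is assumed, not stated. Three of the reasons for 10 years concern the life of the programme, which fits a 10-year entry period with outcomes credited cohort by cohort. On that reading nothing is truncated. This stands as a possible intention, but the disease-lag argument is offered for the same figure and the article never separates the two. It does not remove the conflict with 15 cohorts.

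The model also deals mainly with neonatal and infant illness and with maternal and infant death. Step 5 shows that such events fall inside the window for nearly all of ten annual cohorts. This stands: the cohort-year shares in steps 2 and 3 measure follow-up time, not lost DALYs. Under a fixed window mainly later disability would be cut.

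Fig. 2 is described as adapted from an existing model, so 15 may be a carry-over. That would explain the mismatch without resolving it.

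Stronger readings are tempting, and the documents do not support them:

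- A reader might infer that the plan itself admits the horizon is too short. It concludes the opposite; the shortfall is an inference from its stated lags.
- A reader might infer that years of life lost are also cut at 10 years, so that averted deaths are heavily undercounted. No such rule is stated.
- A reader might carry the 50% difference in births (15 against 10) straight into the ratio. More cohorts add both costs and DALYs, and start-up costs are to be annualized, so the ratio need not move much.
- A reader might infer that the first modelled cohort is wrongly treated as exposed. The year 2011 is that of the baseline survey and may be only a reference year.

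**Conclusion.** The point holds as an inconsistency and an undefined model parameter. The 10-year horizon and the 15 birth cohorts cannot both be right with annual cycles: 10 fit, and 5 of 15 would be born after the window closes. This part rests only on the assumed one-year cycle.

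The second part is conditional. If the 10 years is one fixed calendar window, then for births at the start of each year 1 of 10 cohorts reaches 10 years of follow-up and 4 of 10 do not complete ages 0–5, contrary to the claim of full coverage. Under that reading the cost per DALY averted would tend to be too high, because late cohorts' costs are counted in full and part of their benefit is not. If 10 years means implementation only, with effects credited in full, that bias does not arise.

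The size of any effect on the ratio cannot be derived from the article. The matter should be corrected because it bears on a stated objective, but it leaves the primary coverage analysis intact.

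**What to change.** 1. Make the text of *Costing and cost-effectiveness assessment* and the Fig. 2 note agree on one cohort count that matches the implementation period: 10 annual cohorts if the 10-year programme life is kept. State the cycle length.
2. Define the 10 years as the implementation period, and rest it on the software and programme-life reasons alone.
3. State whether 2011 is only the baseline or reference year, given that the application was introduced in 2012, and which birth year is the first modelled as exposed.
4. Credit each cohort's years of life lost and years lived with disability in full beyond the end of implementation, discounted at the 3% already specified, so that late cohorts' benefits are not cut off while their costs are counted. Use the disease lags to justify this follow-up, not the implementation period.

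The cost is a few sentences and spreadsheet settings. No data collection changes.
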